### 2.7. Randomisation, Treatment Allocation, and Allocation Concealment

Eligible children will be stratified based on the number of carious tooth surfaces at baseline (1 to 3 surfaces vs. more than 3 surfaces) and randomly allocated to receive either 38% SDF solution or gel. Block randomisation with a block size of 6 will be adopted to assign children to the two treatment groups. A statistician who is not involved in the clinical assessment will generate the randomisation sequence and place the group assignments in opaque sealed envelopes. During the clinical examination, once eligibility is confirmed, a research assistant will assign the randomisation envelope sequentially. This approach ensures effective allocation concealment prior to the administration of the assigned SDF intervention.

### 2.8. Blinding

The examiner, the children, and their parents do not know the intervention allocation. This randomised controlled trial will implement a double-blinding approach to reduce bias. The examiner responsible for conducting the oral examinations and assessing the clinical outcomes will remain blinded to the children’s treatment group assignments throughout the study. The group allocation will be determined by a research assistant not involved in the clinical examinations or outcome assessments. Furthermore, the study children and their parents will not be informed of the assigned treatment group. Unblinding is allowed when a parent requests to know their child’s treatment history. In this case, the child will be regarded as withdrawn from this trial.

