### 1.5. Outcome Measures

The primary outcome is the proportion of soft (active) carious tooth surfaces that turn hard (arrested) at the 30-month follow-up. The secondary outcomes are parental satisfaction, children’s compliance, and adverse effects of the SDF therapy.

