### 2.15. Statistical Analysis

Data analysis will be conducted using SPSS 24.0 software (SPSS Inc., Chicago, IL, USA). Intra-examiner agreement for caries diagnosis will be evaluated using Cohen’s Kappa statistics. Non-inferiority of the SDF gel group compared with the SDF solution group (control, caries arresting rate 76.5%) will be accepted if the lower limits of the 95% two-sided CI of the difference in the caries-arresting rate is greater than the non-inferiority margin (7.65%). This test for non-inferiority will only be performed for the primary endpoint, which is the proportion of the soft (active) carious tooth lesion surfaces that turn hard (arrested) at the 30-month follow-up. An intention-to-treat approach is planned to utilise all available data from all originally recruited children.

At subject level, chi-square tests will be used to compare proportions of arrested carious surfaces between groups during the follow-ups. These statistical tests will also be applied to analyse the incidence of new carious surfaces and dropout rates between groups during the follow-ups. Independent sample t-tests will be employed to investigate the differences in the mean values of continuous outcome measures, including the number of newly developed carious surfaces, dmfs scores, and non-vital/hypermobile teeth. Descriptive analyses will be used to report the proportions of adverse effects, as well as the levels of child and parental acceptance for each intervention. The McNemar test will be used to compare the changes in oral-health-related behaviours and children’s cooperation between different treatment groups.

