A multilevel logistic regression model will be employed to account for the clustering effect of multiple carious lesions within individuals. This multilevel model will assess the effectiveness of 38% SDF gel versus 38% SDF solution in arresting active caries at 6, 12, 18, 24 and 30 months, adjusting relevant covariates, such as social-demographic background, oral health-related behaviours, baseline oral characteristics and daily fluoride exposure. By employing this multilevel analytical framework, the study will provide robust evidence on the efficacy of the 38% SDF gel in managing ECC among preschool children. All hypothesis tests will be two-tailed with an α = 0.05 significance level, and they will be conducted according to the pre-specified analyses, adhering to the intention-to-treat principles. Sensitivity analyses will be performed to address any missing data.

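### Counting a child as withdrawn when a parent asks for the treatment history creates avoidable missing 30-month outcomes and undercuts the intention-to-treat aim

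*Protocol article*

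**What the plan says.** Section 2.8 of the protocol article sets a trigger and a consequence. The trigger is: "Unblinding is allowed when a parent requests to know their child’s treatment history". The consequence is: "In this case, the child will be regarded as withdrawn from this trial". The section does not say whether examinations stop, whether data already collected are kept, or how such a child enters the 30-month analysis.

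Section 2.15 says: "An intention-to-treat approach is planned to utilise all available data from all originally recruited children". It later repeats that the tests will be run "adhering to the intention-to-treat principles", and adds: "Sensitivity analyses will be performed to address any missing data".

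Section 1.5 defines the endpoint: "The primary outcome is the proportion of soft (active) carious tooth surfaces that turn hard (arrested) at the 30-month follow-up". Section 2.15 limits the non-inferiority test to that endpoint.

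On assessment, Section 2.8 says that the examiner "will remain blinded to the children’s treatment group assignments throughout the study". Section 2.9 has a different dentist apply the product after the examination is finished.

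**The concern.** A parent's question is an event after randomisation. It is not a withdrawal of consent, and it does not stop the child from being examined. Yet the rule treats it as the end of participation, and a child who leaves before 30 months has no primary outcome. The plan would then rely on sensitivity analyses to repair missing data that its own rule had created.

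Requests may not be random. Parents receive their child's examination results (Data Availability), are asked to report pain and irritation (Sections 2.5 and 2.9), and may be referred for restorative care (Section 2.9). Section 3 expects the two formulations to differ in staining, taste and acceptance, so equal request rates in the two arms cannot be taken for granted. If requests depend on both arm and outcome, the comparison is distorted. Parental satisfaction, a secondary outcome, could also lose dissatisfied parents.

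**Working it through.** **The plan's own figures.** Inputs from Section 2.13: arrest rate 76.5%, margin 7.65 points, two-sided 95% interval, power 90%, 4.75 surfaces per child, ICC 0.227, dropout 20%.

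- Surfaces per arm: 2 × 0.765 × 0.235 × (1.960 + 1.282)² / 0.0765² = 645.6, rounded up to 646; total 1292, as stated.
- Design effect: 1 + (4.75 − 1) × 0.227 = 1.851.
- Evaluable children: 1292 × 1.851 / 4.75 = 503.5, rounded up to 504.
- Recruited: 504 / 0.80 = 630, as stated.

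The sample size is sound on its own inputs. The point concerns follow-up and the analysis population.

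**Standard error.** Effective surfaces per arm: 504 × 4.75 / 1.851 / 2 = 646.6. SE = √(2 × 0.765 × 0.235 / 646.6) = 0.02358.

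**Effect on the non-inferiority error.** Place gel at the margin: 0.765 − 0.0765 = 0.6885. Let a fraction w of an arm be lost through this rule, with arrest rate q among those lost. The rate among those kept is (true rate − w × q) / (1 − w). With d the apparent difference (gel minus solution), the chance of falsely concluding non-inferiority is Φ((0.0765 + d) / 0.02358 − 1.96). The SE is held fixed, which treats these losses as part of the 20% allowance. Every w and q is assumed.

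| Lost, gel / solution | q | Gel kept | Solution kept | d (points) | False non-inferiority |
|---|---|---|---|---|---|
| none | – | 68.85% | 76.50% | −7.65 | 2.5% |
| 5% / 2% | 40% | 70.37% | 77.24% | −6.88 | 5.1% |
| 2% / 5% | 40% | 69.44% | 78.42% | −8.98 | 0.6% |
| 3% / 3% | 40% | 69.74% | 77.63% | −7.89 | 2.0% |
| 5% / 5% | 40% | 70.37% | 78.42% | −8.05 | 1.7% |
| 5% / 2% | 90% | 67.74% | 76.22% | −8.49 | 1.0% |

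Example, second row: gel (0.6885 − 0.05 × 0.40) / 0.95 = 0.7037; solution (0.765 − 0.02 × 0.40) / 0.98 = 0.7724; Φ((0.0765 − 0.0688) / 0.02358 − 1.96) = 0.051.

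A harsher one-sided assumption gives more. If 5% of the gel arm only is lost at 30% arrest, the kept gel rate is (0.6885 − 0.015) / 0.95 = 0.7089, a shift of +2.0 points. With the SE recomputed as √(0.765 × 0.235 / 646.6 + 0.7089 × 0.2911 / (646.6 × 0.95)) = 0.0248, false non-inferiority is about 12.8%.

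**Effect on power.** If the arms are truly equal and 2% gel / 5% solution are lost at 40% arrest, the kept rates are 77.24% and 78.42%. That is a spurious −1.2 points, and power is Φ((0.0765 − 0.0118) / 0.02358 − 1.96) = 78%.

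If losses are balanced, unrelated to outcome and come on top of the 20% dropout, 630 × (0.80 − w) children remain. Power is then 89.3% for w = 2%, 88.1% for 5% and 85.9% for 10%, against 90.0% with no extra loss.

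**The case against.** A reader might infer that Section 2.8 flatly contradicts Section 2.15. The text does not go that far. It does not say that data are deleted or that the child leaves the analysis set. Section 2.15 words intention-to-treat in terms of available data, its multilevel model covers 6 to 30 months, and sensitivity analyses for missing data are promised. Earlier visits can therefore still be used, and a fuller protocol or analysis plan may describe how withdrawals are handled. This stands. It does not rescue the 30-month outcome, however: no analysis plan can recover an examination that was not done.

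A reader might also infer that the rule pushes the result towards non-inferiority. The documents do not support a single direction. Sections 1.2 and 3 present the solution as the product more likely to spill and stain, so requests could come more from that arm. Section 2.9 tells parents that arrested lesions may turn black, so a parent who asks about dark teeth may have a child who responded well. The table shows the error moving either way.

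The claim that such requests would use up the 20% dropout allowance has no support either, since no request rate is documented.

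Finally, continued blinded assessment protects only the examiner's findings. Parental satisfaction and parent-reported adverse events (Sections 1.5 and 2.5) would be open to bias once the parent knows the product. This stands, and the amendment has to deal with it.

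**Conclusion.** The point holds as an unreconciled conflict between a stated withdrawal rule and a stated analysis aim. On its ordinary meaning the rule loses the primary outcome of children who could still be assessed blind and whose parents have not withdrawn consent.

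Its size is unknown. Under modest assumed splits, false non-inferiority ranges from about 0.6% to 5.1% against a nominal 2.5%, with about 12.8% under a harsher gel-only assumption. If requests are few and balanced between arms, the harm is small. These figures rest on assumed request rates and arrest rates, on the 7.65-point margin of Section 2.13, and on the plan's ICC and surface count.

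This is a cheap improvement worth making. It is not a flaw that invalidates the design.

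**What to change.** In Section 2.8, replace the withdrawal sentence with: *The child remains in blinded follow-up and is analysed in the randomised group unless consent is withdrawn; the unblinding, its date and its reason are recorded and reported by arm; the parent is asked not to disclose the allocation to the examiner.*

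In Section 2.15, add a sensitivity analysis of the primary outcome that excludes these children, and state that satisfaction and parent-reported adverse events collected after unblinding will be flagged as unblinded.

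The cost is a short amendment. The 1292 surfaces and 630 children stay as they are. The downsides are a slight risk that a parent reveals the allocation to the examiner, and some parent-reported data collected unblinded. Recruitment began on 1 March 2024 (Section 2.2), so the change is best made early: examinations missed under the present rule cannot be recovered.

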### 2.9. Interventions

After the completion of the oral examinations by the blinded examiner at baseline and follow-ups, another dentist will apply the assigned SDF formulation to all carious lesions. According to the recommended clinical procedures, the dentist will first clean away any food debris from the carious lesions and isolate the carious tooth with gauze or cotton roll.

The dentist will dry the carious lesions with a micro-brush and apply the assigned SDF with another micro-brush on the carious lesions for 60 s. Gauze or cotton roll will be used to absorb excessive SDF [22]. The two intervention groups in this study are the following:

Group A: 38% SDF solution (Advantage Arrest 38% SDF solution, Elevate Oral Care, LLC, West Palm Beach, FL, USA) applied semi-annually, and

Group B: 38% SDF gel (Advantage Arrest 38% SDF Gel, Elevate Oral Care, LLC, West Palm Beach, FL, USA) applied semi-annually.

Children in both groups will be instructed to avoid eating or drinking for 30 min after the SDF application. The SDF therapies will be administered every 6 months for a total duration of 30 months. The parents will be informed to report any potential adverse effects, including tooth pain, allergic reactions, gingival irritation, or other issues related to the SDF treatment within 48 h. Referrals for restorative dental treatment will be provided to the children if deemed necessary. Additionally, both teachers and parents will receive information indicating that successfully arrested carious lesions may appear hardened and turn black following the SDF application.

### 2.10. Assessment of the Children’s Compliance

A trained research assistant will assess the children’s compliance during SDF therapy (solution or gel) using Venham’s behaviour-rating scale. This validated instrument provides six scores to evaluate a child’s reactions and behaviours during dental care [23]. Table 1 shows the codes of Venham’s behaviour-rating scale.

### 2.11. Assessment of Harms

An independent, trained health practitioner instead of the examiner will examine each child one day after the SDF therapy. The health practitioner will record the presence of any post-treatment complications, such as pain in the treated tooth, allergic reactions, gingival irritation, or soft tissue staining around the treated tooth. All harms as an unexpected or anticipated event will be reported to the principal investigator. An assigned dentist will provide emergency consultation and dental care for adverse events. An adverse event refers to an untoward occurrence during the study period, which may or may not be causally related to the SDF therapy or other aspects of trial participation. Any severe adverse events involving hospitalisation or serious injury will be reported to the Institutional Review Board within 7 days. In our previous trials, no children were dismissed or excluded because of adverse effects [24].

### 2.12. Follow-Up Evaluations

The follow-up oral examinations will be conducted semi-annually in the kindergarteners for 30 months by the same examiner using the same equipment, standardised procedure, and diagnostic criteria as used in the baseline examination. The examiner will assess the children’s dmfs index, VPI, the status of carious surfaces (classified as active or arrested through gentle probing), and visible dental plaque at carious lesions. New carious lesions will be recorded and treated with the assigned intervention. An independent, trained health practitioner will examine the children for the presence of potential adverse effects related to the SDF treatments one day after the SDF therapy. Children’s compliance with the SDF therapy will be assessed using Venham’s behaviour-rating scale. Any sign of tooth non-vitality, such as tooth hypermobility or dental abscesses, and reasons for premature tooth loss will be documented.

### 2.13. Sample Size and Power Calculation

In our previous clinical trial, the proportion of active carious surfaces that became arrested after the biannual application of 38% SDF solution over 24 months was 76.5% [25]. We set the non-inferiority margin at 7.65% (which corresponds to 10% of the caries arrest rate observed with the SDF solution). This non-inferiority margin represents a difference between the intervention products that we consider to be clinically insignificant. The estimated sample size is based on the lower limit of the two-sided 95% confidence interval for the difference being set above the non-inferiority margin (−7.65%) and the statistical power of the study being set at 90% (β = 0.10) by the Sealed Envelope Power (sample size) calculators [26].

This non-inferiority trial requires 1292 active-caries tooth surfaces at the 30-month follow-up assessment. We have accounted for the fact that each child may present with multiple carious tooth surfaces, with an estimated mean of 4.75 active-carious surfaces per child and an intraclass correlation (ICC) of 0.227, based on our previous study findings [25]. Furthermore, we have estimated a 30-month dropout rate of 20% and an ECC prevalence of 38% among 3-year-old children, according to the available epidemiological data [27]. Therefore, we will screen approximately 3000 3-year-old children to recruit at least 630 children with ECC, with 315 children assigned to each of the two SDF intervention groups.

### 2.14. Data Management

The collected clinical data will be entered into a Microsoft Excel 2019 file (Microsoft Corp., Redmond, WA, USA) independently by two assistants and cross-checked to minimise errors. They will scrutinise any deviations which can be resolved by consensus. Once the data are entered and verified, the statistician will lock the database. The principal investigator will keep the paper forms in locked cabinets and protect all files with passwords to maintain data security.

### 2.15. Statistical Analysis

Data analysis will be conducted using SPSS 24.0 software (SPSS Inc., Chicago, IL, USA). Intra-examiner agreement for caries diagnosis will be evaluated using Cohen’s Kappa statistics. Non-inferiority of the SDF gel group compared with the SDF solution group (control, caries arresting rate 76.5%) will be accepted if the lower limits of the 95% two-sided CI of the difference in the caries-arresting rate is greater than the non-inferiority margin (7.65%). This test for non-inferiority will only be performed for the primary endpoint, which is the proportion of the soft (active) carious tooth lesion surfaces that turn hard (arrested) at the 30-month follow-up. An intention-to-treat approach is planned to utilise all available data from all originally recruited children.

At subject level, chi-square tests will be used to compare proportions of arrested carious surfaces between groups during the follow-ups. These statistical tests will also be applied to analyse the incidence of new carious surfaces and dropout rates between groups during the follow-ups. Independent sample t-tests will be employed to investigate the differences in the mean values of continuous outcome measures, including the number of newly developed carious surfaces, dmfs scores, and non-vital/hypermobile teeth. Descriptive analyses will be used to report the proportions of adverse effects, as well as the levels of child and parental acceptance for each intervention. The McNemar test will be used to compare the changes in oral-health-related behaviours and children’s cooperation between different treatment groups.

A multilevel logistic regression model will be employed to account for the clustering effect of multiple carious lesions within individuals. This multilevel model will assess the effectiveness of 38% SDF gel versus 38% SDF solution in arresting active caries at 6, 12, 18, 24 and 30 months, adjusting relevant covariates, such as social-demographic background, oral health-related behaviours, baseline oral characteristics and daily fluoride exposure. By employing this multilevel analytical framework, the study will provide robust evidence on the efficacy of the 38% SDF gel in managing ECC among preschool children. All hypothesis tests will be two-tailed with an α = 0.05 significance level, and they will be conducted according to the pre-specified analyses, adhering to the intention-to-treat principles. Sensitivity analyses will be performed to address any missing data.

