### 1.4. Hypothesis

The hypothesis is that the 38% SDF gel is not worse than the 38% SDF solution by a non-inferiority margin of 10% caries arrest rate when applied semi-annually among preschool children.

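### The acceptance rule in section 2.15 sets the lower confidence limit against +7.65% instead of −7.65%, contradicting section 2.13; as written it is not a non-inferiority test

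*Protocol article*

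**What the plan says.** Section 2.15 (Statistical Analysis) holds the decision rule for the primary endpoint. It opens with "Non-inferiority of the SDF gel group compared with the SDF solution group (control, caries arresting rate 76.5%) will be accepted" and sets the condition that the "lower limits of the 95% two-sided CI of the difference in the caries-arresting rate is greater than the non-inferiority margin (7.65" per cent. The figure has no minus sign, and the order of subtraction is not written out.

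Section 2.13 (Sample Size and Power Calculation) first gives the margin as a size: "We set the non-inferiority margin at 7.65% (which corresponds to 10% of the caries arrest rate observed with the SDF solution" group. It then bases the sample size on "lower limit of the two-sided 95% confidence interval for the difference being set above the non-inferiority margin (−7.65" per cent, this time with the minus sign.

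Section 1.4 (Hypothesis) states that "the 38% SDF gel is not worse than the 38% SDF solution by a non-inferiority margin of 10% caries arrest rate".

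**The concern.** Sections 2.13 and 2.15 use the same statistic (the lower limit of a two-sided 95% interval for the difference in arrest rate) and the same size of margin, but opposite signs. A lower limit above a positive margin is a test of superiority by that margin, not of non-inferiority. The section 2.15 sentence decides the trial's primary conclusion. Applied literally, it would fail a gel that is exactly as good as the solution, and the 90% power stated in section 2.13 would belong to a different rule. If the wording were corrected only after unblinding, the success criterion would be changing with the results in hand.

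**Working it through.** **Inputs**

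- Control arrest rate 76.5% and margin 7.65 points, which is 0.10 × 76.5 (section 2.13). The rate comes from the earlier trial: "the biannual application of 38% SDF solution over 24 months was 76.5" per cent.
- Two-sided 95% interval, so 0.025 in the relevant tail (z = 1.960); power 90% (z = 1.282) (section 2.13).
- 1292 surfaces required, 4.75 active surfaces per child, ICC 0.227, 20% dropout, 630 children (section 2.13).
- Equal true arrest rates in the two arms. This is an assumption, and it is the one that reproduces the plan's sample size.

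**Step 1. Reproduce the plan's figures with a limit of −7.65 points**

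- Surfaces per arm = (1.960 + 1.282)² × 2 × 0.765 × 0.235 / 0.0765² ≈ 646, or 1292 in total. This matches section 2.13.
- Design effect = 1 + (4.75 − 1) × 0.227 = 1.851.
- Children = 1292 × 1.851 / 4.75 = 503.5; divided by 0.80 this is 629.4, rounded up to 630. This also matches.

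The trial was therefore sized for a lower limit above **−7.65** points.

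**Step 2. Precision at the planned size**

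SE of the difference = √(2 × 0.765 × 0.235 / 646) = 0.0236, or 2.36 points. The 95% half-width is 1.96 × 2.36 = 4.6 points.

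**Step 3. Probability of passing each rule, difference taken as gel minus solution**

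P(pass) = Φ((d − threshold)/SE − 1.960), where d is the true difference and the SE uses each arm's own rate.

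- At d = 0 and threshold −0.0765: Φ(3.243 − 1.960) = 0.900.
- At d = 0 and threshold +0.0765: Φ(−3.243 − 1.960) ≈ 1 × 10⁻⁷.

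| True gel rate (solution 76.5%) | True difference (points) | Pass, limit −7.65 | Pass, limit +7.65 as printed |
|---|---|---|---|
| 76.5% | 0 | 90.0% | about 1 in 10 million |
| 81.5% | +5 | over 99.9% | 0.09% |
| 84.15% | +7.65 | over 99.9% | 2.5% |
| 86.5% | +10 | over 99.9% | 19% |
| 88.5% | +12 | over 99.9% | 55% |

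Reaching 90% under the printed rule would need a true gel rate of about 90.7%, or 14.2 points better.

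**Step 4. Observed difference needed to pass**

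- Limit −7.65: −7.65 + 4.62 ≈ −3.0 points.
- Limit +7.65: 7.65 + 4.62 ≈ 12.3 points if the variance is held at 76.5% in both arms. If the variance uses the higher gel rate, the half-width falls to about 4.1 points and the requirement is about 11.75 points (gel 88.3% against 76.5%). The gap between the two is only the variance convention.

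**Step 5. Does reversing the subtraction help?**

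No. With solution minus gel, a positive difference means that the gel is worse. A lower limit above +7.65 would then show the gel to be worse by more than the margin, and the rule would call that non-inferiority. In that direction a valid rule uses the *upper* limit, which must lie below +7.65.

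**The case against.** The best case for the plan is that the document already settles the sign. Section 2.13 prints the negative limit, and it also quotes the margin as a positive size one sentence earlier. Section 2.15 can be read as the same shorthand, placed carelessly. The hypothesis in section 1.4 and the description of the design in section 2.1 both exclude a test of superiority by a margin. On this view the near-zero pass probabilities arise only if an analyst follows one sentence against the rest of the document, and no calculation in the plan is wrong.

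Much of this stands. The intent can be recovered, the slip is most likely typographical, and the sample size, power and conduct are unaffected. The probabilities describe the rule taken literally; they do not forecast what the analysts will do. They do not make the printed rule correct, however. Quoting a margin as a positive size is harmless in prose, but not where a lower limit is required to exceed it. Section 2.15 also carries the only acceptance rule in the analysis section, and that section commits to pre-specified analyses.

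It is also true that the Abstract, section 1.4 and the Discussion give the margin as 10%. That concerns the margin's size. Sections 2.13 and 2.15 agree on size and differ only in sign, so settling one question does not settle the other.

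**Conclusion.** The concern holds. The decision rule in section 2.15 contradicts section 2.13 by 15.3 percentage points and is not a valid non-inferiority test under either order of subtraction. Taken literally as gel minus solution, it cuts the chance of success for an equally good gel from 90% to about 1 in 10 million, and to about 19% for a gel truly 10 points better.

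These probabilities rest on the plan's own inputs (76.5% control rate, 4.75 surfaces per child, ICC 0.227, 20% dropout), a normal approximation and unpooled variance. The finding that the sign is wrong depends on none of them. Because the sentence governs the primary conclusion, it must be corrected even though the intended rule can be inferred.

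**What to change.** Replace the condition in section 2.15, and in any analysis plan that repeats it, with wording such as: *Non-inferiority will be accepted if the lower limit of the two-sided 95% CI for the difference in caries-arrest rate (SDF gel minus SDF solution) is greater than −7.65 percentage points.* State the same order of subtraction in section 2.13 so that the two sections match.

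The figure of 7.65 points is the one used in both sections; the 10% stated elsewhere should be reconciled separately.

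The cost is a one-line correction, with no change to sample size, data collection or conduct. It should be dated and in place before unblinding.

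### The sample size allows for clustering of surfaces within children, but the chi-square tests do not, and the non-inferiority interval is not tied to any clustered method

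*Protocol article*

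**What the plan says.** Section 2.7 of the protocol article randomises individual children, stratified by 1 to 3 versus more than 3 carious surfaces. Section 1.5 defines the primary outcome on surfaces: the share of soft surfaces that are hard at 30 months.

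Section 2.13 allows for several surfaces per child, with "an estimated mean of 4.75 active-carious surfaces per child and an intraclass correlation (ICC) of 0.227".

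Section 2.15 then gives three elements:

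- **Decision rule.** "Non-inferiority of the SDF gel group compared with the SDF solution group (control, caries arresting rate 76.5%) will be accepted if the lower limits" of a two-sided 95% interval for the difference in arrest rate lie above the margin. Neither the unit of analysis nor the variance method is given.
- **Chi-square tests.** "At subject level, chi-square tests will be used to compare proportions of arrested carious surfaces between groups during the follow-ups". The same tests are extended to the incidence of new carious surfaces and to dropout.
- **Multilevel model.** "A multilevel logistic regression model will be employed to account for the clustering effect of multiple carious lesions within individuals". It covers 6 to 30 months with covariate adjustment. The text does not say that it supplies the interval for the decision rule, or how its result is put on the margin's scale.

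**The concern.** The method named on the scale of the margin (proportions of surfaces) ignores clustering. The method that handles clustering works on another scale and is not connected to the margin. The trial's single confirmatory claim lies between the two.

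A chi-square test needs a table of counts. A proportion of arrested surfaces, with several surfaces per child, becomes such a table only if surfaces are the units, so the subject-level label does not fit what is tested. An analyst who follows the section as written could easily put an ordinary two-proportion interval beside that test. Such an interval would be too narrow, and the error would favour declaring the gel non-inferior. Leaving the choice open also allows it to be made after the 30-month data are seen.

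**Working it through.** **Inputs.** From Section 2.13:
- control arrest rate 76.5% ("biannual application of 38% SDF solution over 24 months was 76.5")
- margin 7.65 percentage points ("We set the non-inferiority margin at 7.65")
- criterion on the "lower limit of the two-sided 95% confidence interval for the difference", i.e. one-sided 2.5%
- power 90%, 4.75 surfaces per child, ICC 0.227, dropout 20%

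Assumed: a true difference of zero under the alternative. This is not stated, but it is needed to reproduce the plan's figure.

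**1. The plan's own figures.**
- Surfaces per arm = (1.960 + 1.282)² × 2 × 0.765 × 0.235 / 0.0765² = 645.5, so 646; total 1292, as stated.
- Design effect = 1 + (4.75 - 1) × 0.227 = 1.851.
- 1292 × 1.851 = 2392 surfaces; / 4.75 = 503.5 children; / 0.80 = 629.4, so 630, as stated.

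Without the design effect, 1292 / 4.75 / 0.80 = 340 children. The 630 was therefore built for a clustered analysis.

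**2. Width of the interval.** With 630 × 0.80 = 504 completers there are 504 × 4.75 / 2 = 1197 surfaces per arm.
- SE ignoring clustering = √(2 × 0.765 × 0.235 / 1197) = 1.73 points; half-width 1.96 × 1.73 = 3.4 points.
- SE with clustering = 1.73 × √1.851 = 1.73 × 1.361 = 2.36 points; half-width 4.6 points.

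**3. Error if clustering is ignored.**
- One-sided: 1 - Φ(1.96 / 1.361) = 7.5% instead of 2.5%.
- Two-sided (a surface-level chi-square on arrested surfaces): 2 × 7.49% = 15.0% instead of 5%. Equivalently, a nominal 95% interval covers about 85%.

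**4. Simulation check.** Beta-binomial, 252 completers per arm, ICC 0.227, true rates 76.5% and 68.85%, 20,000 runs. With 4 or 5 surfaces per child, the one-sided error was 7.3% for the unclustered interval and 2.4% for a cluster-robust one.

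**5. Sensitivity of the 7.5%.** ICCs other than 0.227, and all coefficients of variation (CV), are assumptions. For unequal numbers of surfaces, design effect = 1 + ((1 + CV²) × 4.75 - 1) × ICC.

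| ICC | CV of surfaces per child | Design effect | One-sided error |
|---|---|---|---|
| 0.10 | 0 | 1.375 | 4.7% |
| 0.15 | 0 | 1.562 | 5.8% |
| 0.227 | 0 | 1.851 | 7.5% |
| 0.30 | 0 | 2.125 | 8.9% |
| 0.227 | 0.5 | 2.121 | 8.9% |
| 0.227 | 0.8 | 2.541 | 10.9% |
| 0.227 | 1.0 | 2.929 | 12.6% |

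The strata in Section 2.7 imply that the number of surfaces varies between children, but the document gives no spread.

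**6. Scale of the model.** A deficit of 7.65 points corresponds to different marginal odds ratios at different control rates:
- 76.5%: (0.6885/0.3115) / (0.765/0.235) = 0.68
- 65%: (0.5735/0.4265) / (0.65/0.35) = 0.72
- 85%: (0.7735/0.2265) / (0.85/0.15) = 0.60

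No single odds ratio stands in for the margin. These are marginal odds ratios; the multilevel model's own odds ratio is conditional on the child and differs again.

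**7. Power with a clustered interval.** Φ(7.65 / 2.358 - 1.96) = Φ(1.284) = 90.0% at 504 completers (simulation, 5,000 runs: 90.4%).

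**The case against.** The strongest reply is that this is a condensed article with no analysis plan shown, and that the variance method for an interval is commonly left to that plan. Clustering is addressed twice, in the sample size and in the multilevel model, so the authors clearly intend to handle it. The chi-square sentence stands in a separate paragraph from the decision rule and tests equality during follow-up; it does not produce the interval that is compared with the margin.

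Much of this stands, and it rules out three stronger readings that a reader might infer:

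- *That the non-inferiority test as planned has a 7.5% error.* No section says that the interval treats surfaces as independent. The 7.5% is conditional on that choice.
- *That the logistic model cannot be compared with a percentage-point margin.* It can: predictions standardised over the trial's children give a risk difference with an interval. That step is unstated, not impossible.
- *That the trial is too small.* The 630 children reproduce only with the design effect.

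The chi-square tests are not covered by this reply. They are stated, not omitted, and an analysis plan that added a clustered interval would leave them wrong for clustered surfaces.

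**Conclusion.** The point holds in this form. The surface-level chi-square tests are a stated error, with about 15% two-sided error at nominal 5% for arrested surfaces, given ICC 0.227 and equal numbers of surfaces per child. For new surfaces the fault is the same if they are counted by surface, but the document gives no ICC from which to size it. The chi-square test for dropout is unaffected, since each child counts once.

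For the non-inferiority decision, the fault is a missing link between the interval and any clustered method. Its possible cost is a one-sided error of about 7.5% instead of 2.5% if clustering were ignored: 4.7% to 8.9% over an assumed ICC of 0.10 to 0.30 with equal clusters, and higher where surfaces per child vary. Because this governs the only confirmatory claim, it should be settled before the 30-month data are analysed.

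**What to change.** In Section 2.15 and the analysis plan:

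- State that the primary analysis is the 30-month risk difference (gel minus solution) with a two-sided 95% confidence interval that accounts for clustering by child, and compare its lower limit with -7.65 percentage points. Either a binomial GEE with identity link and robust standard errors, or risk differences standardised from the logistic model with a bootstrap that resamples children, would serve. Choose one in advance.
- Replace the chi-square tests for arrested and new surfaces with the same clustered method, and remove the subject-level label.
- Keep the multilevel odds ratio as a supportive result.

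The cost is wording and a little programming. The interval will be wider than an unclustered one (half-width 4.6 rather than 3.4 points), but it is the interval for which the sample size was calculated. No extra children are needed.
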